### Outcome measures

#### Primary outcome measure

##### Change of 6MWD from week 24 to week 48 under L-citrulline therapy versus placebo

Several tests have been reported in the medical literature to assess muscle strength and functional ability, to monitor the progression of the disease, and to evaluate the results of drug interventions and rehabilitation. Timed clinical functional assessments include the 6-min Walking Distance Test (6MWD) in meters which is helpful to assess muscle function and fatigue in patients with neuromuscular disorders [16, 17]. The 6MWD is a validated tool to measure the distance that an individual is able to walk over a total of 6 min on a hard, flat surface. The goal for the individual is to walk as far as possible in 6 min. The individual is allowed to self-pace and rest as needed as they traverse back and forth along a marked walkway.

#### Secondary outcome measures

##### Change of MFM scale total score

The MFM scale, a validated assessment tool to measure motor function in both ambulant and nonambulant patients with neuromuscular disorders, was developed in France in 2005. It includes 32 items that evaluate three dimensions of motor performance, including specific motor functions, such as transfers and standing posture (D1), proximal and axial (D2) and distal (D3) and a total MFM score involving all of the motor dimensions. The items are scored and summed to comprise a total score where the maximum represents normal motor function. The instruction manual, validation examinations and other publications using the MFM scale can be downloaded at the MFM scale website [18].

##### Change of quantitative muscle MRI (IDEAL-CPMG with T_2_ and lipid quantitation and dynamic ^31^P-MR spectroscopy)

One of the advantages of muscle MRI imaging methods is that the raw data can be stored and direct comparisons from data at several time points are possible. Visual and semiquantitative muscle MRI studies have been applied in inherited neuromuscular disorders, including SMA, and have identified anatomical abnormality, such as absent, aberrant, or accessory muscles, changes in tissue composition, such as fatty infiltration or increased water content, and masses or mass-like lesions [19, 20]. We use the IDEAL-CPMG sequence allowing simultaneous T_2_ and lipid quantitation and dynamic Phospho-magnet resonance (^31^P-MR) spectroscopy that quantifies the kinetics of phosphocreatine (PCr), ATP and intracellular pH in lower leg muscles during rest, exercise and recovery. As this sequence is not tested previously in an age-correlated group of people without neuromuscular disorders, up to 20 age- and gender-correlated subjects will be examined additionally at one time point.

In neuromuscular disorders, quantitative muscle MRI (qMRI) detects disease progression more sensitively compared to other clinical scores. Excellent reproducibility of qMRI was demonstrated in healthy volunteers as well as in patients [21, 22]. qMRI was more sensitive than clinical evaluation and visual analysis of MRI scans to detect disease progression [20, 23, 24].

##### Change of serum concentrations for markers of muscle necrosis (creatine kinase), oxidative stress (8OHDG, carbonylated proteins 4-Hydroxynonenal (4-HNE)), nitrosative stress (nitrotyrosine, cGMP), and mitochondrial-related genes (*Citratsynthase*, *Cytochrome C oxidase subunit 1*, *Succinate dehydrogenase subunit A*)

Our treatment aims at a stimulation of NO concentrations measured by indirect markers (nitrotyrosine, cGMP), an improvement of the muscular energy situation (citratsynthase, cytochrome C oxidase subunit 1, succinate dehydrogenase subunit A) with reduction of oxidative stress (8OHDG in urine, carbonylated proteins) and a slowing of muscle degeneration (levels of creatine kinase, transaminases, alkaline phosphatase).

#### Auxiliary outcome measures

##### Change of quantitative muscle test (QMT) of elbow flexion, hand grip, knee extension and ankle extension using hand-held dynamometry (HHD)

As the distribution of muscle weakness in PPS patients varies widely, a quantitative muscle testing, including different muscles of the upper and lower limbs, provides probably a more detailed insight into the distribution and evaluation of muscle weakness in each patient.

##### Change of self-report questionnaires SIPP, IBM-FRS and WHOQOL – BREF

The Self-reported Impairments in Persons with late effects of Polio (SIPP) is a new rating scale first published in 2013 and recently reevaluated for test-retest reliability [25, 26]. The IBM-FRS (Inclusion Body Myositis Functional Rating Scale) and the WHOQOL (World Health Organisation – Quality of Life) – BREF questionnaire are widely used and validated scales to assess motor function especially in patients with asymmetric neuromuscular conditions, such as inclusion body myositis, and/or quality of life regardless of any underlying condition [27]. Our aim is to revalidate test-retest reliability of these tests in our patient group and to assess changes compared to other clinical and subclinical outcome measures.

### Randomisation scheme

The study aims to include 15 patients in each of two treatment arms (placebo and verum). A randomisation scheme called Big Stick Design [28] with a maximum tolerated imbalance (MTI) between groups of two patients will be applied. The randomisation corresponds to tossing a fair coin as long as the difference in group sizes does not exceed the MTI. If the MTI is reached, a deterministic allocation is performed so that the difference in group sizes is reduced. For emergency breaking of the group assignment, unblinding envelopes are provided. These envelopes have a window in which only the running patient’s ID is visible and contain an unblinding form that states the patient’s group assignment.

### Sample size estimation

It is assumed that patients in the verum group will on average have a 25% longer 6MWD after 24 weeks of treatment with CIT compared to baseline. It is further assumed that patients in the placebo group will on average have no improvement, but also no deterioration with regard to the 6MWD over the 24 weeks of placebo treatment. For sample size estimation, a data set from a study of patients with Becker’s muscular dystrophy (BMD) treated with the same CIT dose for 6 weeks was used (performed at the University of Basel Children’s hospital, publication in preparation). Patients (mean age 31 years) were assigned to CIT treatment for the duration of 6 weeks and their 6 MWD was measured at baseline and follow-up. Using a resampling method, each sample size *n*
_i=1,…,41_ = 10, …, 50 was evaluated by simulating 999 times *n*
_i_ patients with their 6MWD baseline and follow-up values from a multivariate normal distribution. The multivariate normal distribution was parameterised by the mean 6MWD at baseline from the BMD data set, the mean 6MWD at follow-up (mean baseline value augmented by the expected relative increase *θ*
_i=1,…41_ = 0.1, …, 0.5), and the variance-covariance matrix as estimated from the BMD data set. The patients were randomised in a 1:1 or 1:2 ratio to the placebo and the verum group, respectively, in order to examine the effect of the randomisation ratio on sample size. The resulting data set was analysed with an analysis of covariance (ANCOVA) with 6MWD follow-up measurement as response, 6MWD baseline measurement as adjusting covariate and treatment group (placebo versus verum) as explanatory variable of interest. Finally, it was tested whether there was a difference between the placebo and verum groups.

For an expected mean increase in 6MWD of 25% in the verum group, 28 subjects need to be recruited to obtain 25 evaluable patients, assuming a dropout rate of 10% and when randomising patients 1:1 to placebo and verum, respectively (Fig. 3). To further increase the sensitivity, a similar 24-week run in observational period will be performed in all patients before active or placebo treatment. The latter should help within the placebo group to separate natural history changes from placebo effects during the treatment period.

**Fig. 3 Fig3:**
[figure not shown]
Randomisation placebo:verum 1:1. Association of sample size (*N*) and the mean relative improvement of the verum group in the 6-min Walking Distance Test at follow-up (*θ*), assuming no improvement in the placebo group, for a randomisation ratio of 1:1 into the placebo and verum groups, respectively. Curves are smoothed for illustration purposes only

### Statistics

The full analysis set (FAS) consists of all patients who are randomised and for whom a baseline measurement of the primary endpoint is available. The intention-to-treat (ITT) set is a subset of the FAS that consists of all patients for whom there is a follow-up measurement of the primary endpoint. According to the ITT principle, each patient will be analysed according to the treatment that they are randomly allocated to. The per-protocol (PP) set is a subset of the ITT set that consists of all patients with complete follow-up measurements of the primary endpoint. Each patient will be analysed according to the treatment that they actually receive.

An ANCOVA will be used for the primary analysis. The response variable is the 6MWD after the 24-week treatment period (follow-up). The explanatory variables are the 6MWD at the onset of the treatment period (baseline) and the group (placebo versus verum). The model estimates will be presented together with 95% confidence intervals and *p* values with respect to the null hypothesis that the corresponding estimate has a value of 0. The analysis will be performed on the ITT set. The analysis will be repeated on the PP set and compared to the ITT analysis as a sensitivity analysis.

Following the analysis of the primary endpoint, the secondary endpoints will be analysed as outlined above for the primary endpoint.

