### Study procedure

At screening (visit 1, day −1), patients are informed about preclinical data, alternative treatments, risks and possible benefits of the study. Further, written informed consent is obtained. After signing the Informed Consent Form, inclusion and exclusion criteria are verified. If the criteria are fulfilled, the patient will be enrolled in the study. During the screening visit, the following procedures are performed: 6MWD; vital signs; physical examination; MFM scale. After screening, four visits will be scheduled at baseline (week 0, visit 2), week 24 (visit 3), week 36 (visit 4) and week 48 (visit 5, end of study).

During visit 2 (week 0, baseline), the following procedures are performed: check inclusion/exclusion criteria; vital signs; physical examination; self-report questionnaires; muscle MRI; adverse events; blood draw (laboratory analysis) and urine pregnancy test in women of child-bearing potential. If the patient still qualifies for the study, they will be definitively enrolled in the study. Two weeks after screening, self-report questionnaires are filled in a second time by patients to evaluate the questionnaires for test-retest reliability. During visit 3 (week 24), the following procedures will be performed: 6MWD; vital signs; physical examination; self-report questionnaires; MFM scale; QMT; muscle MRI; adverse events; blood draw (laboratory analysis) and urine pregnancy test in women of child-bearing potential. If the patient still qualifies for the study, they will be randomised and receive the study medication or placebo accordingly. During visit 4 (week 36), the following procedures are performed: 6MWD; vital signs; physical examination; MFM scale; QMT adverse events; blood draw (laboratory analysis); dispensing of study medication; collection of boxes with sachets of used study medication for compliance control. During the last visit (visit 5, week 48, end of study), the following procedures are performed: 6MWD; vital signs; physical examination; self-report questionnaires; MFM scale; QMT; muscle MRI; adverse events; blood draw (laboratory testing); collection of boxes with sachets of used study medication for compliance control. The full planned visiting and examination schedule is provided in Fig. 2.

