### Ethical considerations

PPS is a serious progressive neuromuscular disease with no therapy so far. Affected patients suffer from severe impairment that justifies an attempt to improve this condition using an almost side-effect-free treatment.

The participation in this study is voluntary. If the patients do not want to participate, they will not experience any disadvantages concerning any further medical treatment. The same applies if the patients withdraw the consent at a later time point. They have this possibility at any time. Possible withdrawal of consent from the study can occur without giving any reason. In case of withdrawal the data collected until this time point will be used and the samples (blood) collected in the context of the study will be destroyed. In case of withdrawal the patient will undergo a final visit for a medical examination for his own safety.

A placebo group is necessary to demonstrate the efficacy of the used medication (CIT) and to exclude a possible placebo effect.

There is a great potential that positive results of this study could lead to other large multicenter trials. Furthermore, if we can show an effect of CIT on muscle function, this will be a major breakthrough and mean a better symptomatic treatment of the muscle degeneration that occurs in PPS.

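### The primary analysis set labelled ITT is a completer set: randomised patients without a follow-up 6MWD enter no stated analysis, even if they walked at week 36

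*Protocol article*

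**What the plan says.** All of the analysis rules are in the Statistics section of the protocol article.

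- The FAS "consists of all patients who are randomised and for whom a baseline measurement of the primary endpoint is available".
- The ITT "set is a subset of the FAS that consists of all patients for whom there is a follow-up measurement" of the primary endpoint. The sentence on the ITT principle that follows covers only analysis by allocated arm.
- The per-protocol (PP) "set is a subset of the ITT set that consists of all patients with complete follow-up measurements of the primary endpoint".
- Primary model: "The response variable is the 6MWD after the 24-week treatment period (follow-up"). The bracketed word ties *follow-up* to week 48. The only other terms are the 6MWD at the onset of treatment and the group.
- "The analysis will be performed on the ITT set", and the PP set provides the one stated sensitivity analysis.

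Under Study procedure, patients are randomised at week 24 and the walk is also taken on treatment at week 36: "During visit 4 (week 36), the following procedures are performed: 6MWD". Randomisation and blinding states that dropouts after week 24 are not replaced. Sample size estimation assumes 10% dropout.

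**The concern.** The three sets are nested: FAS, then ITT, then PP. Only the two inner sets are analysed, and both require a follow-up walk. Whether a patient has that walk is decided after randomisation. Safety assessments lists noncompliance, abnormal laboratory results and abnormal rises in blood pressure among the reasons for ending participation early, and any of these could differ by arm. The comparison labelled ITT is therefore not fully protected by randomisation, and with 15 patients per arm each loss counts.

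The sensitivity analysis cannot reveal the problem, because the PP set omits the same patients. A reader of the eventual report would also take ITT to mean that everyone randomised was analysed.

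**Working it through.** **1. The plan's own figure.** 25 evaluable / (1 − 0.10) = 27.8, rounded up to 28, which agrees with the text. The plan thus expects 28 − 25 = 3 patients without an outcome (also 10% of the planned 30). The 10% is not split by arm or by period, so some of it may fall in the 24-week run-in before randomisation. Three is therefore an upper planning figure for loss after randomisation.

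**2. Who is analysed.** A randomised patient with a week-24 and a week-36 walk but no week-48 walk is in the FAS. If follow-up means week 48, the patient is outside ITT and PP. If *a follow-up measurement* is read to admit a week-36 walk, the patient is in the ITT set but has no value for the model's single response. Such a patient contributes nothing on either reading, and on the second the set and the model do not match.

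**3. Possible size.** The article gives no mean, SD or correlation for the 6MWD, so these are assumptions: mean 400 m, SD 100 m at each visit, correlation 0.85 between week 24 and each later visit, week 36 to week 48 correlation *c* of 0.85 or 0.90, 15 per arm, no true effect. The patients lost are those with the worst change at week 36.

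- SD of the week-36 change: 100 × √(2 × 0.15) = 54.8 m (variance 3,000).
- Covariance of that change with the baseline-adjusted week-48 walk: 10,000 × [(*c* − 0.85) + 0.85 × 0.15] = 1,275 or 1,775.
- Slope: 1,275/3,000 = 0.425, or 1,775/3,000 = 0.592.
- Expected lowest three of 15 standard normal values: −1.736, −1.248, −0.948. Removing 1, 2 or 3 raises the mean of those kept by 1.736/14 = 0.124, 2.984/13 = 0.230 or 3.932/12 = 0.328 SD, which is 6.8, 12.6 or 18.0 m of week-36 change.
- Bias = slope × shift: 2.9, 5.3 or 7.6 m (*c* = 0.85); 4.0, 7.4 or 10.6 m (*c* = 0.90). For 2 verum and 1 placebo, subtract: 5.3 − 2.9 = 2.4 m, or 7.4 − 4.0 = 3.4 m.

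A simulation of the stated ANCOVA (20,000 trials per cell) agrees:

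| Lost (verum/placebo) | Bias, *c* = 0.85 | Two-sided rejection | Bias, *c* = 0.90 | Two-sided rejection |
|---|---|---|---|---|
| 3/0 at random | −0.1 m | 5.2% | −0.1 m | 5.1% |
| 1/1 worst change | 0.0 m | 5.3% | 0.0 m | 5.6% |
| 2/1 worst change | +2.5 m | 5.3% | +3.5 m | 6.1% |
| 1/0 worst change | +2.9 m | 5.4% | +4.1 m | 5.7% |
| 2/0 worst change | +5.4 m | 5.9% | +7.6 m | 6.9% |
| 3/0 worst change | +7.7 m | 6.8% | +10.8 m | 8.6% |

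**4. What week 36 recovers.** A likelihood estimate that uses the week-36 walk stays within 0.2 m of zero in every row. With three worst-change verum losses and *c* = 0.85, its SD is 20.8 m against 20.5 m for the completer ANCOVA, so it costs almost no precision. This is the favourable case, because the simulated loss depends only on walks already observed.

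**The case against.** The strongest reply concerns size. The largest figures need three losses, all on verum and all with poor week-36 results. Even then, 8 to 11 m is about 0.4 to 0.5 of a standard error of roughly 20 m. It is 8 to 11% of the planned effect, which is 25% of the assumed 400 m, or 100 m. With random or balanced loss there is no bias. All of this stands, and it means that the documents do not show a material bias at the plan's own expected loss.

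The article is also a condensation, and the choice of imputation method or covariance structure may properly sit in an analysis plan. That stands for such details. It does not excuse the set definitions, response, model and sensitivity set, which the article states and which together fix a completer analysis.

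A reader might infer more than the documents support:

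- **A contradiction with Ethical considerations.** That section says "In case of withdrawal the data collected until this time point will be used". The sentence concerns keeping data after consent is withdrawn, as against destroying blood samples. It promises nothing about the primary model.
- **Secondary endpoints lose patients for lack of a 6MWD.** The article says only that they are analysed in the same way as the primary endpoint. Each may be meant to use its own follow-up value. The wording is open, not wrong.
- **A stated dilution of the 25% gain.** Any such figure assumes that every lost patient was on verum and gained nothing, which the article does not say.
- **A missing walk should count as 0 m.** Nothing in the article supports such a rule.

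**Conclusion.** The point holds as a mislabelled and badly chosen primary analysis set. No stated analysis includes a randomised patient who lacks the follow-up walk, the FAS is defined and left unused, and a scheduled on-treatment measurement is ignored. This follows from the text and needs no assumption.

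The size does need assumptions. Under those listed, the bias runs from 0 m (random or balanced loss), through about +2 to +8 m (two verum and one placebo, or one to two verum only), to about +8 or +11 m (three verum, worst week-36 change). In the last case two-sided rejection is about 7 to 9% against a nominal 5%. The direction reverses if the selective loss is on placebo. Loss during the run-in does not bias the randomised comparison.

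**What to change.** - Make the FAS the primary analysis set, analysed as randomised, and define it by the 6MWD at the onset of treatment (week 24). The present definition says only baseline, a word that the Fig. 2 legend attaches to screening values.
- Estimate the week-48 difference from a repeated-measures model of the week-36 and week-48 6MWD, adjusted for the week-24 value. Alternatively, use the stated ANCOVA after multiple imputation that includes week 36.
- Rename the present ITT set *completers* and keep it as a sensitivity analysis.
- State that each secondary endpoint is analysed on the FAS and does not depend on whether a 6MWD is available.

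The cost is revised wording, a few more model parameters and slightly more analysis work. No visit or measurement is added. Two limits remain. A patient with no walk after week 24 adds almost nothing to either method, and loss that depends on unobserved week-48 results is not fully corrected. The change should be made before unblinding.

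### The per-protocol set is defined by 6MWD data availability alone, so comparing it with the ITT run cannot show the effect of non-adherence or protocol violations

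*Protocol article*

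**What the plan says.** All of the following is in the protocol article.

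- **ITT set (Statistics).** "The intention-to-treat (ITT) set is a subset of the FAS that consists of all patients for whom there is a follow-up measurement"; the measurement meant is the 6MWD. Patients are analysed as randomised.
- **Per-protocol set (Statistics).** "The per-protocol (PP) set is a subset of the ITT set that consists of all patients with complete follow-up measurements"; here too the 6MWD is meant. A further sentence adds: "Each patient will be analysed according to the treatment that they actually receive".
- **Role of the per-protocol run (Statistics).** "The analysis will be repeated on the PP set and compared to the ITT analysis as a sensitivity analysis". The article names no other sensitivity analysis. Secondary endpoints are to be analysed in the same way.
- **Primary endpoint (Outcome measures).** "Change of 6MWD from week 24 to week 48 under L-citrulline therapy versus placebo". The ANCOVA in Statistics takes the 6MWD at the end of the 24-week treatment period as response, with the value at treatment onset and the group as explanatory variables.
- **Visits (Study procedure).** On treatment, the 6MWD is measured at week 36 (visit 4) and week 48 (visit 5). Both visits include "collection of boxes with sachets of used study medication for compliance control".
- **Other compliance information.** Quality assurance says the returned boxes serve to assess intake. Safety assessments lists noncompliance as a protocol violation that can lead to early termination. Quality control has the monitor check eligibility criteria and drug accountability.

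**The concern.** A per-protocol set normally answers one question: does the result hold among patients who were eligible and took the treatment broadly as planned? Here the set is selected only on whether the outcome was measured, and the primary model already selects on nearly the same condition. A patient who took few or no sachets, or who should not have been enrolled, counts as per protocol once the walks are recorded.

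What is at stake is interpretation. If the two runs agree, a reader will tend to take this as evidence that non-adherence and violations did not drive the result. With this definition the agreement carries no such evidence. In a trial of about 30 patients taking sachets three times a day for 24 weeks, a few poor adherers could dilute the estimate, and the named comparison would not reveal it.

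**Working it through.** **The article's own figure.** Sample size estimation gives 25 evaluable patients at 10% dropout: 25 / (1 − 0.10) = 27.8, rounded up to 28. This matches the stated 28. Planned enrolment is 30, and 30 × 0.90 = 27, which is used below as the number with a week-48 walk. The point does not depend on these figures.

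**Set logic.** The article states no imputation, so a patient without a week-48 walk cannot enter the ANCOVA. Reading A takes *complete* to mean that week 48 is present. Reading B requires weeks 36 and 48. All patients below are randomised and have a treatment-onset walk.

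| Patient | ITT-set ANCOVA | PP, reading A | PP, reading B |
|---|---|---|---|
| Both walks, full intake | in | in | in |
| Both walks, little or no intake | in | in | in |
| Both walks, eligibility or other major violation | in | in | in |
| Week 48 only | in | in | out |
| Week 36 only | out | out | out |
| Neither walk | out | out | out |
| Both walks, given the other arm's product | in, randomised arm | in, arm received | in, arm received |

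The runs separate in two rows only: week 48 only (under reading B) and wrong product. The rows for poor intake and for violations are the same in every column.

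**Illustration by simulation.** None of these inputs comes from the article, apart from 27, which is derived above: baseline mean 400 m, SD 100 m, correlation 0.9 between baseline and follow-up, effect 50 m in adherent verum patients and 0 m in non-adherent ones, non-adherence at random in either arm, 4000 runs per row. Both ANCOVAs were fitted to each data set, together with one that drops the non-adherent patients.

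| Non-adherent of 27 | Missed week 36 only | Wrong product | ITT mean (m) | PP as written (m) | Correlation of the two | Mean absolute difference (m) | Non-adherent dropped (m) |
|---|---|---|---|---|---|---|---|
| 0 | 0 | 0 | 49.7 | 49.7 | 1.000 | 0.00 | 49.7 |
| 0 | 1 | 0 | 50.1 | 50.1 | 0.981 | 2.71 | 50.1 |
| 0 | 3 | 0 | 50.1 | 50.1 | 0.937 | 5.09 | 50.1 |
| 5 | 0 | 0 | 40.6 | 40.6 | 1.000 | 0.00 | 50.0 |
| 5 | 1 | 0 | 40.7 | 40.8 | 0.977 | 2.91 | 49.9 |
| 5 | 3 | 0 | 40.9 | 40.8 | 0.937 | 5.31 | 50.3 |
| 5 | 0 | 1 | 37.6 | 40.9 | 0.924 | 6.16 | 46.0 |

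As a check on the fourth row, 50 × (1 − 5/27) = 40.7 m, in line with the simulated 40.6 m.

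With all visits attended and no wrong product, the two runs are identical whether 0 or 5 patients are non-adherent. Missed week-36 visits add scatter but no average shift. With 1 to 3 such patients the two runs fell on opposite sides of p = 0.05 in about 5% to 13% of data sets. That is noise from dropping patients and carries no information on adherence.

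**On the article's effect scale.** If 3 of 15 verum patients take nothing and gain nothing, an assumed 25% gain in takers becomes 25% × 12/15 = 20%. With all walks recorded, both runs estimate this same 20%. The 3 of 15 is hypothetical.

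**The case against.** A reader might infer that the per-protocol run repeats the primary result by construction and that agreement is automatic. The text does not support that. The sentence right after the definition makes the per-protocol run as-treated, so a single dispensing error can separate the runs (mean absolute difference about 6 m in the illustration). If *complete* includes week 36, a missed visit 4 separates them too. This objection stands, and the point is limited accordingly. It does not rescue the comparison as a check on adherence: the as-treated rule sorts patients by the product received, with no threshold for how much was taken.

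A second objection is that the contrast between one follow-up measurement and complete measurements may mean that the ITT set keeps patients with partial follow-up, with a missing week 48 handled in the full protocol or analysis plan. The per-protocol set would then be a completers set, and the comparison would say something about missing data. This is possible, although the stated response variable favours the narrower reading. It would still say nothing about adherence or violations. For the same reason, the absence of a missing-data sensitivity analysis from this article is not part of the point.

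Third, adherence cut-offs and deviation lists often sit in an analysis plan. That is fair for details left open. Here the article gives a rule for the set, and the rule rests on outcome availability alone.

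Fourth, safeguards exist: eligibility is rechecked before randomisation, the monitor reviews eligibility and drug accountability, and noncompliance can end participation. These make violations less likely and poor intake visible in the records. None of them enters the definition, and a non-adherent patient who is not withdrawn stays in both runs.

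**Conclusion.** The point holds in limited form. As written, the ITT and per-protocol runs use essentially the same patients. They can differ only through a week-48 walk without a week-36 walk (reading B) or through receipt of the other arm's product. The comparison cannot show the effect of non-adherence or protocol violations, and agreement should not be reported as robustness to them.

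This conclusion rests on the stated definitions and on no imputation in the ANCOVA, not on the illustrative figures. The 40.6 m against about 50 m, and the fall from 25% to 20%, are assumptions put through arithmetic. The article gives no rate of missed week-36 visits, so the number of patients by which the sets would differ cannot be derived. Zero to 2 of 27 would be a guess.

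A reader might also infer that the primary result is biased. It is not, on this account: under non-adherence the diluted estimate is the ordinary as-randomised effect, and the primary ANCOVA, its estimate and its p value are untouched. The defect lies in the supportive analysis and in what may be claimed from it. It should be corrected because the correction is cheap.

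**What to change.** Before unblinding, redefine the per-protocol set as randomised patients who:

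- met the eligibility criteria;
- reached a pre-specified level of sachet intake, by the returned-box counts at visits 4 and 5;
- had no major protocol deviation, from a list fixed in advance; and
- have a week-48 6MWD.

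Say explicitly whether a week-36 walk is required. Classify patients while the treatment code is still closed. Label the analysis supportive, because it selects patients after randomisation and those who adhere may differ between arms. The simulation assumed non-adherence at random and therefore does not show this risk. Apply the same set wherever the secondary endpoints repeat the analysis.

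The cost is wording in the analysis plan, since the sachet returns and drug accountability are already collected. The downside is a smaller per-protocol set with a less precise estimate.
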